### 2.3. Sample Size Considerations

With a hypothesized difference of 20% in change scores (from baseline to the four-time points) for each of the primary outcome variables of interest (e.g., mean change score of 10 vs. 8), a population variance of 5.0 for the mean change score, a 2-sided significance level (α = 0.05), a power of 90% and an acceptable difference between the sample mean and population mean score for each scale of zero (μ − μ0 = 0), an estimated sample size of 131 participants in each arm of the study would be needed (based on the 6Sigma online script) to detect the projected mean differences in mean change scores between the intervention and control groups [29,30]. Thus, the sample size for the RCT would be 262. Given that the maximum survey completion rate for the online surveys delivered via text message is approximately 20%, in order to achieve 262 completed survey responses at each time point, we plan to enrol at least 1500 participants in the RCT. This recruitment rate is achievable since a related study in Alberta [31] currently has over 500 patients recruited within six months. The sample size for the qualitative component of the study cannot be predetermined. Data saturation is reached across data analysis, ending when no new themes and subthemes emerge. However, based on what the literature suggests [32,33], we anticipate that 25–30 participants may be sufficient for this particular mixed-method study.

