### 2.6. Outcome Measures

The intervention effectiveness will be determined by evaluating the differences between the intervention and control group from baseline and the subsequent time points (6 weeks and 3, 6, and 12 months) for patient clinical outcomes and the differences between groups for health service utilization at 12 months, and the implementation success will be measured through quantitative and qualitative patient satisfaction data and implementation indicators, as follows:Clinical outcomes: The primary clinical outcome will be the differences in mean change in patient recovery and quality of life, assessed through the Recovery Assessment Scale (RAS) [37] and the World Health Organization Five Well-Being Index (WHO-5) [38]. Secondary clinical outcomes will include the differences between the intervention and control groups in prevalence changes for moderate-to-high depression (likely major depressive disorder), moderate-to-high anxiety (likely generalized anxiety disorder), and low resilience from the baseline to these time points, assessed through the Patient Health Questionnaire-9 (PHQ-9) [39], Generalized Anxiety Disorder-7 scale [40], and the Brief Resilience Scale (BRS) [41]. The mean score differences between groups from the baseline to determine time points will also be assessed using the Adverse Childhood questionnaire (ACE questionnaire) [42], and the Brief Substance Use Craving Scale (BSCS) [43], which will be used to assess childhood trauma and substance craving, as well as the clinician-rated Columbia-Suicide Severity Rating Scale (C-SSRS) [44], which will be used to assess suicide risk.Health service utilization outcomes: Health service utilization data will be extracted by the registration, reporting, and analytics, mental health and addiction team from the multiple health information systems utilized across NS Health and provided to the research team through reports. The differences in health service utilization data (mobile crisis visits, number of ED presentations, number of admissions in the last 12 months, length of stay, and the number of hospital readmissions) will be evaluated for participants in both groups. The differences between groups will be evaluated at 12 months.Patient experience and satisfaction outcomes: Patient satisfaction and patient experience with the e-mental health interventions (Text4Support and other e-mental health programs offered freely through NSH Authority) will be evaluated using both quantitative and qualitative data. Overall satisfaction will be assessed at each of the four time points (6 weeks and 3, 6, and 12 months) using a self-designed scale. Self-reported retention and withdrawal will both be assessed through the satisfaction survey, which addresses questions about the frequency of reading messages, the frequency of returning to messages stored in their phones, and actions taken by the participants after reading the text messages or freely available e-mental health resources (i.e., text “STOP”, clicking on links, searching for more information) up to 12 months after enrolment. Patient experience and satisfaction qualitative data will be collected through individual interviews and focus groups.Implementation Outcomes: Implementation outcomes are indicators of implementation efforts and are distinct from service or clinical outcomes [45]. For the intervention arm, we will include the reach of the interventions, acceptability, appropriateness, fidelity, and cost-effectiveness, evaluated at each of the four time points [28]. These implementation indicators will not be collected from the e-mental health or website visits in the control arm because they are not tied to the patient’s study ID and cannot be linked to the other measures.

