Patient satisfaction quantitative data will be analyzed by using one-way analysis of variance (ANOVA) tests to compare satisfaction between the two study groups. Likert scale satisfaction responses to various aspects of Text4Support and freely accessible Health-Authority-approved low-intensity e-mental health services will be summarized as frequency counts of response categories and percentages. We will compare the differences in satisfaction between the groups by using the Chi-square/Fisher exact test with two-tailed criteria. A Bonferroni-corrected, two-tailed criterion (α = 0.05/*n* (*n* = number of comparisons) will be used to determine statistical differences.

Qualitative data analysis will be aligned with qualitative descriptive methods. The qualitative data analysis will be guided using the six-phase thematic analysis framework [26] and conducted by two distinct members of the research team. They will perform an independent analysis and then compare their findings. Data disagreements will be resolved by discussion and convergence, if possible. The remaining disagreements will be resolved by a third researcher and/or documented for discussion in the study report.

The first step of qualitative analysis is to transcribe verbatim all audio records from the semi-structured individual interviews and focus groups and enter them in NVIVO 12 [48] software for data organization and preparation. This step is crucial to becoming familiar with the data, and reading and re-reading the transcripts. At this stage, we will also perform data validation for quality assurance purposes. A data validator, who is a different person from the transcriber, will compare the verbatim transcriptions with the recorded interviews for verbal and non-verbal errors (commissions and omissions). Errors in transcription will be corrected during validation. The subsequent phases of thematic analysis (coding, searching for themes, themes review, themes definitions, and writing) will be accomplished [27]. The sample size for the qualitative sub-study will depend on data saturation [32,33].

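### Satisfaction is compared between arms by two tests with no rule for which decides, and the one that follows the Likert counts ignores category order

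*Protocol article*

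**What the plan says.** The relevant text is the satisfaction paragraph of section 2.7 (Data Analysis) in the protocol article. It makes four statements in turn.

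- The between-arm comparison: "Patient satisfaction quantitative data will be analyzed by using one-way analysis of variance (ANOVA) tests to compare satisfaction between the two study groups".
- The Likert items: "Likert scale satisfaction responses to various aspects of Text4Support" and of the control arm's e-mental health services "will be summarized as frequency counts of response categories and percentages".
- Directly after that, a second between-arm comparison: "We will compare the differences in satisfaction between the groups by using the Chi-square/Fisher exact test with two-tailed criteria".
- The significance level: "A Bonferroni-corrected, two-tailed criterion (α = 0.05/*n* (*n* = number of comparisons) will be used to determine statistical differences".

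Section 2.6 adds the timing: "Overall satisfaction will be assessed at each of the four time points", namely 6 weeks and 3, 6 and 12 months, on a self-designed scale. The closing paragraph of the Introduction lists patient satisfaction among the secondary aims. No test for ordered categories (rank-sum, trend or proportional odds) is named.

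**The concern.** Both named tests address the same question, whether satisfaction differs between the arms. The paragraph does not say which data go to which test, or which result counts if they disagree.

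The order of the sentences attaches chi-square/Fisher to the Likert category tables. On an uncollapsed table with k ordered categories and two arms, Pearson's test has k − 1 degrees of freedom and asks whether the distributions differ in any way. Shuffling the category labels leaves the p-value unchanged. Four consequences follow:

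- A consistent shift towards higher satisfaction is spread over several degrees of freedom, so power falls. The Bonferroni criterion is then applied on top.
- A significant result may mean that one arm gave more extreme answers at both ends, not that it was more satisfied.
- A two-tailed criterion has no directional meaning for this statistic when there are more than two categories.
- The test gives no estimate of how much satisfaction differs.

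At stake is a secondary aim. The primary outcomes are not touched.

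**Working it through.** **Inputs from the article.** Section 2.3 states that "an estimated sample size of 131 participants in each arm of the study would be needed". Allocation is 1:1 (section 2.1). Alpha for satisfaction is 0.05/n, with n not given. The number of Likert categories and a satisfaction effect size are also not given, so they are assumptions below.

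**The plan's own figure.** Section 2.3 uses a difference of 2 (change of 10 against 8), a spread of 5.0, two-sided alpha 0.05 and 90% power, for the primary scales only. With 5.0 as an SD, n per arm = 2(1.960 + 1.282)² × 5²/2² = 131.3, which matches the stated 131. With 5.0 as a variance, the label the article gives it, n = 2(1.960 + 1.282)² × 5/2² = 26.3, or 27. The 131 therefore corresponds to a standardised effect of 2/5 = 0.4. The literal variance would give 2/√5 = 0.89. Neither was chosen for satisfaction, so 0.4 SD serves only as an illustrative moderate shift.

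**Analytic check.** A one-directional shift gives a 1-df ordered test noncentrality λ. If the unordered test has the same λ on k − 1 df, its power is P(χ²(k − 1, λ) > critical value). At alpha 0.05, 80% power on 1 df needs λ = (1.960 + 0.842)² = 7.85. On 4 df (five categories) the same λ gives 59.5%, a loss of 20.5 points. Where the ordered test has 50 to 90% power, the loss is:

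- 7 to 11 points with three categories
- 12 to 17 points with four
- 16 to 22 points with five
- 23 to 29 points with seven

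**Simulation, proportional-odds shift.** 131 per arm, alpha 0.05, five categories, 6000 runs per setting. The control distributions were (.1,.2,.4,.2,.1), (.05,.1,.2,.4,.25), uniform, and (.03,.05,.12,.4,.4). The table gives the range of power (%) over the four.

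| Odds ratio | Chi-square | Wilcoxon | ANOVA | Wilcoxon minus chi-square (points) |
|---|---|---|---|---|
| 1.5 | 24.6–26.9 | 42.2–45.6 | 37.4–45.8 | 17.5–18.6 |
| 1.75 | 43.1–50.6 | 66.6–72.4 | 60.6–72.3 | 21.8–23.6 |
| 2.0 | 63.0–71.2 | 82.4–88.7 | 77.7–88.5 | 17.5–19.4 |
| 2.5 | 88.3–93.0 | 96.9–98.6 | 94.5–98.6 | 5.5–8.6 |
| 3.0 | 97.1–98.5 | 99.6–99.8 | 98.8–99.8 | 1.3–2.5 |

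With three categories (.2,.3,.5) the loss is 8.4 to 10.1 points for odds ratios 1.5 to 2.0 and 1.2 points at 3.0. At an assumed Bonferroni level of 0.05/4 = 0.0125 with five categories, the loss is 12 to 25 points for odds ratios 1.5 to 2.0 and 4 to 8 points at 3.0.

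**Simulation, latent normal shift of 0.4 SD.** Five categories, 131 per arm, alpha 0.05, three control distributions: (.05,.10,.25,.40,.20), (.10,.20,.40,.20,.10) and (.03,.05,.12,.40,.40). Chi-square power is 0.68, 0.68 and 0.61, against 0.86, 0.87 and 0.81 for Wilcoxon. A separate run that included the ANOVA gave Wilcoxon 0.848, 0.855 and 0.804, and ANOVA 0.846, 0.866 and 0.796. With 150 per arm (20% of 1500 is 300), chi-square has 0.72, 0.75 and 0.67 against 0.89, 0.91 and 0.85. At 0.89 SD with 131 per arm, all the tests have power above 99% and the loss vanishes.

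**Where the ANOVA stands.** It has essentially Wilcoxon power in most settings. In the table's scenarios the largest shortfall is for the most skewed distribution: 66.6 − 60.6 = 6.0 points at alpha 0.05 (odds ratio 1.75), and 66.9 − 59.6 = 7.3 points at 0.0125 (odds ratio 2.0).

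**The case against.** The strongest reply is that the plan already contains a test that uses the order. With two arms, one-way ANOVA is a t-test on the scores. It has a direction, compares means and keeps nearly all of the Wilcoxon power. That stands, and it rules out two stronger readings that a reader might infer. One is that the plan as a whole ignores the order of the answers, which is not so. The other is that it cannot show which arm is more satisfied. The chi-square statistic alone cannot, but the planned percentages and the ANOVA means can.

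A second reply is that the power figure rests on inputs the article does not give. That also stands. Over the settings examined the loss runs from about 1 to 29 points, so no single figure is a property of the plan.

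Third, the article does not say that the table is left uncollapsed. A two-tailed Fisher test is natural for a 2×2 table, and section 2.6 shows that the survey also covers actions such as texting STOP or clicking links, for which chi-square/Fisher is suitable. So the point is conditional. But the sentence before the test speaks of counts by response category, and nothing mentions collapsing.

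Fourth, the allocation of items to tests and the Bonferroni count can be left to a statistical analysis plan, and chi-square on Likert counts is a valid test with correct type I error. Both are fair, and the absence of those details is not the point. The article itself names two tests for one comparison, and the one placed next to the Likert items suits ordered data less well than an equally simple alternative.

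**Conclusion.** The point holds as a minor one. Section 2.7 gives two between-arm tests of satisfaction without saying which decides, and the test that follows the Likert counts ignores order if run on the uncollapsed table.

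Assuming five categories, 131 responders per arm, alpha 0.05 and a moderate one-directional shift, that test gives up roughly 17 to 24 points of power against an ordinal test. The loss shrinks to about 10 points or less with three categories and to 1 to 3 points at an odds ratio of 3. It disappears for binary items. The planned ANOVA largely escapes it. The figure therefore describes one of the two named tests under stated assumptions, and should not be read as the loss of the trial's satisfaction analysis. Satisfaction is a secondary aim with no power calculation of its own, so this is a cheap improvement and not a threat to the trial's main conclusions.

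**What to change.** Replace the chi-square/Fisher sentence in section 2.7 with wording such as: Ordinal Likert satisfaction items will be compared between groups by a Wilcoxon rank-sum test [or: by a proportional-odds model reporting the common odds ratio with its 95% CI]; this is the deciding comparison for these items. Chi-square or Fisher exact tests will be used for binary items only. Frequency tables are descriptive.

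Choose one of the two bracketed options in advance. The proportional-odds model has the advantage of giving an effect estimate. If the ANOVA is kept, state which data it applies to (for example, a summed score) and that it does not compete with the deciding test for the single items.

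The cost is a sentence or two of analysis wording. It needs no extra data, visits or participants, and standard software suffices. The only loss is slightly lower sensitivity to differences without a direction, which the satisfaction aim does not ask about.

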### 2.7. Data Analysis

Quantitative data will be analyzed in concordance with the CONSORT guidelines [46]. The baseline demographic and clinical characteristics of the two groups will be analyzed using Chi-squared, Fisher’s Exact, and Student’s *t*-tests. The primary (clinical mental health outcomes) and secondary outcome (health services utilization) measures will be analyzed using descriptive and inferential statistical analysis, and Bonferroni correction will be used when necessary. The scores at each time point on standardized rating scales for clinical variables (PHQ-9, GAD-7, WHO Five Well-Being Index, BRS, RAS, ACE, C-SSRS, and BSCS) will each be compared between the intervention and control groups using an analysis of covariance (ANCOVA) with the treatment condition as the independent variable, the baseline scores on clinical variables as the covariate, and the scores at each time point on standardized rating scales as the dependent variable. In each case, checks would be conducted to ensure the reliable measurement of the covariate and no violation of the statistical assumptions of normality, linearity, homogeneity of variance, and homogeneity of regression slopes. Multiple imputations will be our baseline approach to addressing missing data, although analysis of missingness patterns must be performed to inform our specific assumptions, implementation, and interpretation during missing data analysis. Sensitivity analyses will also be conducted with respect to the imputation approach, including a comparison with the last observation carried forward, mean/median imputation, best case, worst case, and complete case analyses. The reasons for discrepancies between approaches will be analyzed and discussed in the study manuscript. We will also compare the prevalence scores for the clinical variables of interest using Chi-square/Fisher’s exact tests. To explore the impact of select demographic and clinical variables on the clinical variables of interest, we will perform a two-way between-groups = analysis of variance. Characteristics of individuals/clusters will be summarized by exposure status to allow the consideration of selection biases and lack of balance [47]. In terms of the number of multiply imputed datasets to be analyzed, we will begin with 100 datasets. A sensitivity analysis will subsequently increase this number to ascertain the stability of model estimates in relation to the number of multiply imputed datasets.

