## 3. Expected Results

The results of this study are expected within three years after the project initiation. Based on previous research [13,14,15,16,17,18,19,20], we anticipate that Text4support in Nova Scotia will achieve similar mental health outcomes, with a 20% greater improvement in patients’ recovery and quality of life and a 20% greater reduction in depressive and anxiety symptoms, when assessed by the mean change in validated scale scores at six weeks and three, six, and twelve months from the baseline compared with control interventions. The mean differences in scores obtained from other validated scales that will assess resilience, childhood trauma, substance craving, the presence and severity of psychotic disorders, suicide risk, and manic symptoms are expected to be alike. We also anticipate a 10–25% reduction in high-cost health service use (psychiatric readmissions and ED visits) among Text4Support participants compared with the usual care group. An unpublished pilot trial in Alberta (*n* = 180) found that the patients discharged from inpatient psychiatric units who received Text4Support messages for 6 months made 10% fewer ED visits in the 6 months following discharge than a control population [6]. We anticipate that Text4Support participants will also use fewer high-cost health services in Nova Scotia. In terms of the retention and patient engagement rates, we confidently predict that IG participants will achieve higher figures (at least 80%) than the CG participants’ self-reported retention rate and engagement on e-mental health resources. This optimistic estimation is based on evidence of “push” text message technologies, in which intervention messages are delivered without the individual’s intervention and have a 98% open rate [49]. Additionally, previous research has shown that after six weeks of intervention, the retention rate in similar text messaging programs (Text4Hope) was around 90% [17,18], indicating that subscribers were still opening and reading the messages.

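### Bonferroni is the only multiplicity method the plan names; Holm's step-down would give the same family-wise error control and never reject less (optional improvement)

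*Protocol article*

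**What the plan says.** All the text on multiplicity is in Section 2.7, Data Analysis, of the protocol article, and it differs by outcome.

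- **Clinical and service-use outcomes.** "Bonferroni correction will be used when necessary". No family, divisor or triggering condition is given. The same paragraph compares each rating scale between arms at each time point by ANCOVA.
- **Patient satisfaction.** After the ANOVA and the chi-square or Fisher comparisons, the paragraph closes by setting "A Bonferroni-corrected, two-tailed criterion", with α equal to 0.05/n and n the number of comparisons. The value of n is not given. Section 2.6 adds: "Overall satisfaction will be assessed at each of the four time points (6 weeks and 3, 6, and 12 months").

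No other multiplicity procedure is named. Section 2.6 makes RAS and WHO-5 the primary clinical outcome. Section 3, Expected Results, forecasts a 20% greater improvement in recovery and quality of life, "when assessed by the mean change in validated scale scores at six weeks and three, six, and twelve months".

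**The concern.** Single-step Bonferroni holds every comparison in a family of n to 0.05/n, whatever the other comparisons show. Holm relaxes the threshold after each rejection, at no cost to the error bound. For the decision to reject or not, Bonferroni is therefore dominated.

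The difference is largest when most hypotheses in a family are false, and Section 3 forecasts that pattern for the two primary scales. What is at stake is power to show benefit on several scales and time points from the same data. The validity of any positive result is not in question.

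**Working it through.** **1. Why Holm is never worse.** Order the p-values. Holm compares the k-th smallest with 0.05/(n − k + 1) and stops at the first failure.
- Every Holm threshold is at least 0.05/n, so any p-value that passes Bonferroni also passes Holm, as do all smaller ones.
- Suppose the first true null rejected is at step k. Then at most n − k + 1 nulls are true, so its p-value is at most 0.05 divided by the number of true nulls. By the Bonferroni inequality this has probability at most 0.05, under any dependence.
- For n = 8 the Holm thresholds are 0.00625, 0.00714, 0.00833, 0.0100, 0.0125, 0.0167, 0.025 and 0.05. Bonferroni uses 0.00625 throughout.

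**2. The plan's own figure (Section 2.3).** The inputs are a difference of 2 points (10 vs. 8), two-sided α = 0.05, power 90%, and a stated population variance of 5.0. The formula is n per arm = 2(1.960 + 1.282)² σ²/δ².
- Variance 5.0 as written: 2 × 10.507 × 5/4 = 26.3, so 27 per arm. This does not reproduce 131.
- 5.0 read as the SD: 2 × 10.507 × 25/4 = 131.3. This approximately reproduces the stated 131.

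The second reading gives a standardised effect of 2/5 = 0.4.

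**3. Single-comparison power at 131 per arm.** The test statistic has mean 0.4 × √(131/2) = 3.237.
- At α = 0.05: Φ(3.237 − 1.960) = 90%.
- At α = 0.05/8 = 0.00625: Φ(3.237 − 2.734) = 69%.

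**4. Bonferroni against Holm, 8 tests.** The family is assumed: two primary scales × four time points. Correlated normal test statistics were simulated with equal effects of 0.4.

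| Effects that are real | Correlation | Mean power, Bonferroni | Mean power, Holm |
|---|---|---|---|
| All 8 | 0.3 / 0.5 / 0.7 | 69.3 / 69.2 / 69.2% | 81.4 / 80.2 / 78.8% |
| 4 of 8 | 0 / 0.5 | 69.3 / 69.2% | 73.0 / 72.4% |
| 1 of 8 | 0 / 0.5 | 69.2 / 69.2% | 69.3 / 69.2% |

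- All eight declared, all real, correlation 0.3–0.7: 18–38% with Bonferroni, 52–66% with Holm.
- At least one declared, all real, correlation 0.5: 96.8% with both, because Holm's first step is Bonferroni.
- Family-wise error with no real effect, correlation 0.5: 4.0% with both. With four real effects and independent tests: 2.5% with Bonferroni, 4.0% with Holm. All are within 5%.

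**5. Smaller family.** With the two primary scales at one time point, both real and correlation 0–0.5, mean power is 84.1% with Bonferroni and 88.2–89.0% with Holm.

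**6. If 5.0 really is the variance.** The SD is 2.236 and the standardised effect is 2/2.236 = 0.894. The statistic's mean is 0.894 × √(131/2) = 7.24, and power at 0.00625 is Φ(7.24 − 2.73) = Φ(4.51), above 99.9%. Holm then has nothing left to gain.

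**The case against.** The strongest reply is that nothing here is wrong. Bonferroni is a valid, common and conservative prespecified rule, the article never claims that it is the most powerful one, and it gives simple simultaneous confidence intervals. That stands, and it is why this is only a suggestion.

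Three further points also stand.
- **Scope.** A reader might infer that the plan fixes 0.05/n for the primary scales. It does not. The explicit divisor closes the satisfaction paragraph, directly after "We will compare the differences in satisfaction between the groups by using the Chi-square/Fisher exact test with two-tailed criteria". For the clinical and service-use outcomes the correction is conditional and no family is set, which may be left to an analysis plan not shown.
- **Where the figures apply.** The power figures above are for clinical scales. The article gives no effect size for satisfaction, so no gain can be computed for the one analysis where 0.05/n is written.
- **Best case.** The 10–12 point gain needs all eight effects to be real and equal. That includes 12 months, by when, under Section 2.5, the messages have been over for six months.

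What the reply does not remove is that Bonferroni is the only method named, so wherever a correction is applied it is the less powerful of two rules with the same error guarantee. Section 2.7 does not call for simultaneous intervals, so their simplicity buys little here.

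**Conclusion.** The point holds as a cheap, optional improvement. Holm keeps the same 5% family-wise bound and never rejects less.

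The size depends on assumptions the article does not settle: a family of 8, 131 respondents per arm, and 5.0 read as an SD. On those, mean power per comparison rises from 69% to 79–81% if every effect is real, by about 3–4 points if half are, and by about nil if one is. The chance of at least one rejection is unchanged when all effects are real. If 5.0 is truly a variance, there is no gain.

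It would be tempting to say that the plan discards real effects for nothing. The document does not support that: the gain can be nil, and the simpler simultaneous intervals are a genuine, if unused, advantage of Bonferroni.

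**What to change.** In Section 2.7, wherever a Bonferroni correction would be applied, use Holm's step-down within the same family. Order the n p-values, compare the k-th smallest with 0.05/(n − k + 1), stop at the first failure, and report Holm-adjusted p-values. This covers the satisfaction comparisons and any clinical or service-use family for which a correction is judged necessary. Make the change before unblinding.

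The cost is a sentence of wording, with no extra participants or data. The one downside is that simultaneous confidence intervals are less direct than under Bonferroni. Unadjusted 95% intervals can be shown beside the adjusted p-values, labelled as unadjusted because the two will not always agree.
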